### Specifically the study will

• Evaluate uptake of the 'Quit with Practice Nurse' intervention versus the referral intervention and the control group in terms of the number of patients, demographics, socio-economic status, language and ethnicity, smoking history and level of nicotine dependence. *Hypothesis: the 'Quit with Practice Nurse' intervention will reach more smokers because it will meet the needs of a greater range of smokers with different demographic, socioeconomic and cultural characteristics than referral model or standard in-practice GP management*.

• Compare the effect on cessation of 'Quit with Practice Nurse' versus 'Quitline Referral' and the control group. *Hypothesis: the 'Quit with Practice Nurse' model will achieve higher quit rates as more patients will receive a cessation intervention that meets their individual needs*.

• Examine the cost effectiveness of the three approaches and their components from the perspective of the health care sector. *Hypothesis: the more intensive intervention may be more costly than usual care or 'Quitline Referral' but any higher costs of the 'Quit with Practice Nurse' intervention will be justified by its higher uptake and quit rate*.

• Assess the acceptability to patients of the 'Quit with Practice Nurse' intervention. *Hypothesis: the 'Quit with Practice Nurse' intervention will be acceptable to patients as it offers a flexible package of support to meet patient needs*.

• Assess acceptability and sustainability of practice nurse assisted support to quit from the perspective of practice nurses and GPs. *Hypothesis: the 'Quit with Practice Nurse' intervention will be acceptable to practice nurses and GPs as it provides an important new role for practice nurses and provides GPs the option of referral within their practice*.

## Methods/Design

This study is a three arm cluster randomised trial involving general practices with practice nurses located in Sydney and Melbourne, which are Australia's two largest cities. Recruitment will expand if necessary to other parts of New South Wales and Victoria. Practices will be allocated to one of three groups 1) Quit with Practice Nurse 2) Quitline Referral 3) usual care control group.

### Recruitment

#### General practice recruitment

Practices which employ at least one practice nurse will be eligible to participate. Eligible practices will be identified with the assistance of local general practice networks (local GP organisations). All GPs working in these practices will be approached by mailing an initial invitation letter followed by a telephone call from one of the chief investigators. GPs expressing interest on the phone will be visited by project staff to explain the project to GPs and practice nurses and to gain informed consent.

Randomisation to intervention groups will follow procedures outlined in the CONSORT statement [36] and will be performed by a researcher independent of the project team. Randomisation will occur in permuted blocks of size three using a system of sealed envelopes. Following randomisation, practices are notified of their allocation prior to the commencement of patient recruitment. Practices in the control group are given copies of smoking cessation guidelines [11]. Practices in the active referral arm are in addition given copies of active referral sheets with which to make referrals to the Quitline. Practices in the 'Quit with Practice Nurse' group are scheduled for the practice nurse to attend the one day training course (see below).

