#### Data Analysis

Analysis for the primary outcomes of sustained abstinence and point prevalence abstinence will be on an intention to treat basis with cases retained regardless of whether they accept or receive the intended intervention. A series of planned imputation strategies for missing data will be used in examining outcomes for missing data. These are 1) analysis will be done on all participating patients, where all patients with missing outcome data will be assumed to be smokers; 2) the last known value carried forward to replace the missing value; 3) an analysis of outcomes for patients with complete outcome data. We will compare cessation outcomes between the three arms at three months and 12 month follow-up using multiple logistic regression. This approach will allow us to adjust for clustering and to assess the effect of potential confounders such as age, sex, socioeconomic status, ethnicity, language spoken at home and nicotine dependence on cessation outcomes.

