#### Sample size

The observed 12 month sustained abstinence outcomes of GP usual care and Quitline referral in Borland et al.'s study in Victoria were 2.6% and 6.5% respectively [16]. The sustained abstinence at six months in a pilot study of practice nurse support was 16%. Assuming this drops to 12% at 12 months we have calculated power to detect a 5.5% difference in sustained abstinence quit rates between 'Quit with Practice Nurse' intervention versus the referral intervention and a 9.4% difference between 'Quit with Practice Nurse' intervention and the usual care control group at one year follow up with 80% power at the 5% significance level. Before adjustment for clustering this requires 471 patients per group to detect the 5.5% difference and 140 per group to detect the 9.4% difference (calculations using STATA software). To adjust for clustering the intracluster correlation coefficient observed by Lennox et al. in a smoking cessation trial in general practice has been used. The intracluster correlation coefficient observed in this study was 0.013 [45]. The resulting design effect = [1+ (size of cluster-1) × intracluster correlation]. In this study we plan to recruit 25 patients per practice so the design effect is 1.31 so the number per arm is 471 × 1.31 = 617 giving a total sample size of 1851. To enroll these participants we will recruit 90 general practices and 2250 patients across New South Wales and Victorian study locations (to allow for approximately 10% drop out rate of practices) and randomise 30 practices to each arm of the study.

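### No stratification by state is named and every named covariate is patient-level: stratifying and adjusting for state would be a cheap gain in precision and balance

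*Protocol article*

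**What the plan says.** Methods/Design places the practices in Sydney and Melbourne and adds: "Recruitment will expand if necessary to other parts of New South Wales and Victoria".

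General practice recruitment gives the allocation method: "Randomisation will occur in permuted blocks of size three using a system of sealed envelopes". An independent researcher carries it out, following CONSORT procedures. No stratification factor is named. All practices learn their allocation before patient recruitment starts. Control and referral practices receive written materials, whereas nurse-arm practices "are scheduled for the practice nurse to attend the one day training course". The nurse training section adds that Quitline counsellors attend the sessions. Under Patient recruitment, each practice has one two-week window.

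Data Analysis specifies multiple logistic regression that adjusts for clustering and assesses "potential confounders such as age, sex, socioeconomic status, ethnicity, language spoken at home and nicotine dependence". City, state and recruitment date are not among the examples.

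Sample size plans 30 practices per arm and 25 patients per practice, with an intracluster correlation (ICC) of 0.013. The trial is sized on the nurse-referral contrast, 12% against 6.5%.

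**The concern.** The practice is the unit of randomisation, and state is a practice-level factor known before allocation at no cost. It could be prognostic here. The planning rates for usual care and referral come from a study in Victoria alone, and the Quitline is all of one intervention and part of another. Whether quit rates or Quitline delivery differ by state is not stated.

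With 30 practices per arm, a visible difference in state mix can easily arise. If state matters for abstinence, that difference adds noise to each contrast, and it invites doubt about comparability when the baseline table is published. Both are avoidable.

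Timing is a secondary matter. Blocks of three balance the date of randomisation, not the date on which patients are recruited. Only the nurse arm has a scheduled step between the two. The 12-month endpoint requires at least 10 months of abstinence, so it credits only quits begun in about the first two months after enrolment. A difference in calendar window between arms could therefore reach the primary outcome.

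**Working it through.** **1. The plan's own figures.** Inputs from Sample size: "with 80% power at the 5% significance level"; usual care and referral rates "were 2.6% and 6.5% respectively"; for the nurse arm, "Assuming this drops to 12% at 12 months". Sidedness is not stated; two-sided is assumed.

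- Without continuity correction, n = [1.96·√(2·p̄(1−p̄)) + 0.84·√(p1(1−p1) + p2(1−p2))]² / d². This gives 435 per group for 12% v 6.5% and 120 for 12% v 2.6%, rounding up.
- With the correction, n' = (n/4)·[1 + √(1 + 4/(n·d))]². This gives 471 and 140, matching "this requires 471 patients per group to detect the 5.5% difference and 140 per group to detect the 9.4% difference".
- Design effect = 1 + 24 × 0.013 = 1.312. Then 471 × 1.31 = 617 per arm, and 617 × 3 = 1851.

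The sample size reproduces, and nothing below changes it.

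**2. Chance imbalance by state.** Assume 90 practices, 45 per state, entering in random order, in unstratified blocks of three.

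- The difference between two arms in the number of practices from one state has variance 60 × 0.5 × 0.5 × 90/89 = 15.17, so SD = 3.9 practices, or 13 percentage points of 30.
- Simulation (40,000 randomisations): a given pair of arms differs by 6 or more in about 16%, and at least one of the two nurse contrasts does so in about 27%. For a 30/60 split the figures are about 13% and 23%.

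**3. Effect on the nurse-referral contrast.** At the planned 30 × 25 = 750 per arm, SE = √[1.312 × (0.065×0.935 + 0.12×0.88)/750] = 1.71 points. The shift due to state has SD = gap × 3.9/30, and its share of the variance is (SD/1.71)². The gaps are assumptions, and any state difference is counted inside the ICC.

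| State gap in abstinence | SD of shift | Share of variance |
|---|---|---|
| 1 point | 0.13 points | 0.6% |
| 2 points | 0.26 points | 2% |
| 3 points | 0.39 points | 5% |
| 4 points | 0.52 points | 9% |

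**4. How large can the gap be?** At the mean of the two rates, 9.25%, the ICC implies a between-practice variance of 0.013 × 0.0925 × 0.9075 = 0.00109. In an even mix a gap g contributes (g/2)². A 4-point gap contributes 0.0004, or 37% of that variance; a 6-point gap contributes 0.0009, or 82%. At the mean across all three arms (about 7%) the total is 0.00085, and a 6-point gap exceeds it. Gaps above 4 points therefore fit the plan's own ICC poorly.

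**5. Type I error.** Simulation of a practice-level t test: two arms, 30 practices each, 25 patients per practice, abstinence 8%, ICC 0.013, 20,000 replicates.

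| State gap | Unstratified, no state term | Unstratified, state term | Stratified, no state term |
|---|---|---|---|
| 3 points | 5.0% | 5.2% | 4.4% |
| 5 points | 5.0% | 5.0% | 3.2% |

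The nominal level holds without stratification or adjustment. Stratifying without a state term makes the test conservative, so the two changes belong together.

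**6. Timing.** No arithmetic is possible, because the article gives neither a delay nor a time trend.

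**The case against.** The strongest reply is that this is read from silence. A condensed article may omit stratification, and separate envelope sets by city would fit its wording. The covariate list is open, so a state term is not ruled out and may sit in an analysis plan that is not shown. This stands in part: the point cannot be put as an established omission. But the article does give block size and concealment, and a stratification factor would normally appear in that same sentence. The point is therefore conditional on the sequence being unstratified.

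Second, a reader might infer that ignoring place biases the trial. The documents do not support that. Under randomisation, state mix differs between arms only by chance, and the planned adjustment for clustering carries that variation in the standard error. Step 5 confirms it.

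Third, an imbalance of 6 practices moves the estimate by gap × 6/30. That is 0.4 points for a 2-point gap and 0.8 for a 4-point gap, or 7% and 15% of the 5.5-point target. These are tail figures that apply in about one randomisation in six, and they rest on assumed gaps. The variance shares in step 3 measure the expected cost better.

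Fourth, a reader might infer that nurse-arm practices recruit later because they wait for the workshop. If so, the difference would be systematic, and a cluster-adjusted standard error would not cover it. But nothing in the article says that recruitment waits for training, how long any wait lasts, or that the other arms start sooner. It remains a possibility to settle, not a finding of bias.

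**Conclusion.** A cheap improvement, not an error. The allocation method as described is valid, the stated sample size is unaffected, and type I error is preserved. If the sequence is unstratified and state is left out of the model, the trial gives up about 0.6% to 9% of the variance of its main contrast for state gaps of 1 to 4 points. It also runs about a 16% chance that a given pair of arms differs by 6 or more of 30 practices in state mix.

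These figures rest on an assumed even split between states, practices entering in random order, 25 patients per practice, and assumed gaps counted inside the ICC of 0.013. If abstinence does not differ by state, only face balance is gained. The timing point cannot be sized from the article.

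**What to change.** - **Allocation:** keep a separate envelope sequence for each state, and name state as the stratification factor under General practice recruitment.
- **Model:** add state as a prespecified term in the logistic regression under Data Analysis. If randomisation has started, make this change alone.
- **Timing (secondary):** say when each arm starts patient recruitment relative to randomisation and to the workshop. Where feasible, let the practices of one block recruit in the same weeks, and include recruitment period in the model or in a sensitivity analysis.

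Cost: two envelope sequences instead of one, possibly incomplete final blocks that leave the arms slightly uneven, some scheduling work, and one or two model terms. Aligning windows could also mean that control and referral practices wait for their block's nurse-arm practice. No extra practices or patients are needed.

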#### Patient recruitment

Eligible patients are those aged 18 and over presenting to their GPs who are daily or weekly smokers. Potential participants will be excluded if they meet any of the following criteria: unable to give informed consent (poor physical and/or cognitive state), insufficient command of English to comprehend the consent process and/or data collection questions. A research assistant will be attached to each participating practice for a two week recruitment period and approach patients in the waiting room prior to the consultation with the GP. Initially the research assistant will assess patient eligibility and, if eligible, patients will be given a copy of participant information statement. Patients providing a written consent will be asked to complete the baseline data questionnaire at this time. Patients take notice of their participation into the GP consultation. GPs respond to this notification depending on their group allocation.

This method of recruitment maintains a separation of baseline data collection from the intervention. Waiting room recruitment has previously been used successfully by members of the research team in studies on smokers, [37,38] risky drinkers [39] and overweight and obese patients [40].

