#### Outcome measures

Patient level measures will be assessed at baseline, three months and 12 months (the schedule of data collection is shown in table 2. At baseline patients will be asked to complete a paper questionnaire assessing demographics including age, sex, language spoken at home, ethnicity, education levels, occupation, current level of smoking, nicotine dependence, quitting history and presence of co-morbidities. Three month and 12 month data will be collected by Computer Assisted Telephone Interview (CATI) by trained interviewers who are blind to intervention group until after the outcome data is collected.

**Table 2 T2:** Schedule of data collection

	At recruitment	3-months	12-months
Age, gender, language spoken at home,	X		
Smoking history	X	X	X
Nicotine dependence	X	X	X
Sustained abstinence		X	X
Point prevalence abstinence		X	X
Quit attempts			X
Intervention costs		X	X
Process evaluation data from patients			
Process evaluation data from PN, GPs and Quitline counselors			X

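### Patients are enrolled after practices learn their arm, by a recruiter not stated to be masked, and readiness to quit is not among the listed common baseline items

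*Protocol article*

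**What the plan says.** *General practice recruitment* fixes the order of events: "Following randomisation, practices are notified of their allocation prior to the commencement of patient recruitment". Arm-specific arrangements follow at practice level. For the Quitline arm, "Practices in the active referral arm are in addition given copies of active referral sheets". For the nurse arm, "Practices in the 'Quit with Practice Nurse' group are scheduled for the practice nurse to attend the one day training course".

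*Patient recruitment* then describes enrolment: "A research assistant will be attached to each participating practice for a two week recruitment period and approach patients in the waiting room". The same person screens and informs: "Initially the research assistant will assess patient eligibility and, if eligible, patients will be given a copy of participant information statement". Consent and the baseline questionnaire come before the GP consultation, and GPs act according to their arm once the patient brings notice of participation. The section draws one reassurance from this: "This method of recruitment maintains a separation of baseline data collection from the intervention".

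Masking is mentioned once, in *Outcome measures*, for follow-up at 3 and 12 months by "trained interviewers who are blind to intervention group until after the outcome data is collected".

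The same section lists the baseline items as demographics together with "current level of smoking, nicotine dependence, quitting history and presence of co-morbidities". Readiness to quit is not among them. It appears only in the description of the Quit with Practice Nurse intervention, as something the nurse records at the first visit. The example covariates in *Data Analysis* are age, sex, socioeconomic status, ethnicity, language and nicotine dependence.

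**The concern.** Cluster randomisation makes the practices comparable. It does not by itself make the patients comparable when they are identified and consented later, in a setting that already knows its arm. If the arms enrol different mixes of motivated and unmotivated smokers, the difference in quit rates contains a selection component that looks like a treatment effect.

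Three features make this worth attention here:

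- Any adult daily or weekly smoker is eligible, so enrolled patients may range from uninterested to ready to quit. Motivation is a plausible strong predictor of the outcome.
- Motivation is not listed as measured in a common way across arms before the intervention. The one listed measurement comes after enrolment and in one arm only, so it cannot serve for comparison or adjustment.
- *Primary outcomes* includes uptake and patient characteristics by group. Differential enrolment would affect that outcome directly, as well as the cessation rates.

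**Working it through.** **1. The passages side by side.**

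- Practice learns its arm: before patient recruitment (*General practice recruitment*).
- Patient approached, screened and consented, baseline completed: afterwards, in that practice, before the consultation (*Patient recruitment*).
- Masking at enrolment: none stated. Masking at outcome: stated (*Outcome measures*).
- Readiness to quit at baseline in all arms: not listed. At the nurse's first visit in one arm: listed (*Quit with Practice Nurse*).

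Taking baseline data before the intervention protects the answers to the questionnaire. It does not bear on who is approached or who agrees.

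**2. The plan's own targets.** *Sample size* gives 12-month sustained abstinence of 2.6% (usual care), 6.5% (Quitline) and 12% (nurse). The targets are 12 − 6.5 = 5.5 points and 12 − 2.6 = 9.4 points. With two-sided 5% significance, 80% power and a continuity correction, the two-proportion formula returns the stated 471 and 140 per group (435 and 120 without the correction). The design effect is 1 + (25 − 1) × 0.013 = 1.312, and 471 × 1.31 = 617 per arm. These figures reproduce and are not disputed. They serve only as a yardstick.

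**3. Illustration on assumed inputs.** The documents give no quit rate by motivation and no expected imbalance. Assume no treatment effect, 12-month quit rates of 12% in ready and 3% in other smokers, and an excess of 10 to 30 percentage points of ready smokers in the nurse arm.

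Shift = excess × (12% − 3%)

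- 0.10 × 9 = 0.9 points; 0.30 × 9 = 2.7 points.
- Nurse versus usual care: 0.9 / 9.4 = 10%; 2.7 / 9.4 = 29%.
- Nurse versus Quitline, if the imbalance lay between those arms: 0.9 / 5.5 = 16%; 2.7 / 5.5 = 49%.

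A limit on these inputs: any mix of 12% and 3% gives at least 3%, which is above the 2.6% planned for usual care. The 6.5% planned for Quitline would correspond to (6.5 − 3) / 9 = 39% ready smokers. The assumed rates therefore fit the level of the Quitline contrast better than that of usual care.

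**4. Sensitivity to the assumptions.** Take 40% motivated in one arm and 50% to 70% in the other, with quit rates (motivated, other) of (10%, 3%), (12%, 2%) or (15%, 3%), again with no true effect.

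- Smallest spurious difference: 0.10 × (10 − 3) = 0.7 points, 13% of 5.5.
- Largest: 0.30 × (15 − 3) = 3.6 points, 65% of 5.5.

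For the false-positive rate, the effective size is 617 / 1.312 = 470 per arm, SE = √[2p̄(1 − p̄)/470], and the rate is Φ(d/SE − 1.96) + Φ(−d/SE − 1.96).

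- Smallest: rates 5.8% and 6.5%, SE 1.57 points, d/SE 0.45, rate about 7%.
- Largest: rates 7.8% and 11.4%, SE 1.92 points, d/SE 1.87, rate about 47%.

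The nominal rate is 5%. This range comes entirely from the assumed inputs.

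**The case against.** The design carries real protection. The person who approaches patients and judges eligibility is a research assistant, not the GP or nurse who has been told the arm. The criteria are broad and leave little discretion: age, smoking frequency, ability to consent and adequate English. Interest in quitting is not required. Consent precedes the consultation, and arm-specific handling is described as starting with the GP. All this stands, and it leaves self-selection at consent, or uneven approach by a recruiter who has learned the arm, as the remaining routes.

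The order of notification also has a reason. Patients go straight from consent to a GP who must act by arm, in one arm with a trained nurse to refer to. Practices need their allocation by then.

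Three stronger readings are tempting, and the article does not support them:

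- A reader might infer that the recruiter knows the arm. The article says neither that the assistant knows it nor that the assistant is masked. Two weeks in a practice that knows its arm makes masking hard to sustain, but that is inference.
- A reader might infer that patients in the nurse arm are invited with a promise of nurse support. No such approach is described. The wording of the information statement and the keeping of a screening log are details that a condensed article may leave to the full protocol, so their absence is not held against it.
- A reader might infer that an imbalance would be invisible and beyond adjustment. Quitting history, smoking level and nicotine dependence are recorded in all arms, patient characteristics are reported by group, and the covariate list is given as examples. A gross imbalance could show in part. These items are proxies, however, and do not replace a direct measure of readiness.

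**Conclusion.** The point holds as a risk that the listed data can address only in part. Disclosure to practices before enrolment is stated text. The absence of stated recruiter masking is silence, and no imbalance has been shown. The existing safeguards reduce the risk of differential enrolment by motivation without removing it, and the one variable that would show it directly is listed in one arm only, after enrolment.

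The size cannot be derived from the documents. The illustrative shift of 0.9 to 2.7 points rests on assumed quit rates and an assumed imbalance. The share must be matched to the contrast: the 16% to 49% range applies only if the imbalance lies between the nurse and Quitline arms, and for nurse versus usual care it is 10% to 29%. The figures show only that, at expected quit rates of 2.6% to 12%, a moderate imbalance in motivation would not be negligible.

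**What to change.** - Add one readiness-to-quit item to the baseline questionnaire that patients in all arms complete before the consultation, and prespecify it as a covariate in the logistic regression.
- Keep the research assistant unaware of the practice's allocation where feasible, and use the same approach to patients in every arm. The common approach also protects the new item, since a patient who has learned the arm might answer it differently.
- Report by arm the numbers of smokers approached, eligible and consenting.

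The order of notification need not change. The cost is one questionnaire item, a small ethics amendment and the keeping of counts, with no extra staff. Masking inside the practice may sometimes fail; the readiness item and the counts would still make an imbalance more visible, and the item would allow adjustment for it.
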